## Abstract

**Background:**

Somatropin treatment is indicated in a variety of disorders including growth hormone (GH) deficiency, Prader–Willi and Turner syndrome, chronic renal insufficiency and others. To date, almost all studies have been limited to single GH products, and no independent registry across indications and somatropin products was ever established.

**Aim:**

The present investigator-initiated registry named INSIGHTS-GHT aims to provide comprehensive information on various aspects of somatropin treatment in Germany in approved indications within routine clinical practice: drug utilization, effectiveness (including real final height, body composition), tolerability, quality of life, other patient related outcomes (PRO), and health economic variables.

**Methods:**

Registry (prospective observational study) in specialised pediatric and adult endocrinology centres in Germany. Patients of any age are eligible for documentation, if they are on ongoing or newly initiated treatment with any approved somatropin or somatropin-related product within the labelling, available for long term follow-up documentation, and if they provided informed consent. Subjects may switch, discontinue/interrupt or initiate somatropin products at any time. They are followed up for at least 3 years (minimal study duration). Documentation is planned once or twice per year to record somatropin utilisation (product, dosing), other medications, laboratory status (glucose, lipids, GH function including stimulation tests, IGF-I, IGFBP3), if applicable, pubertal development, auxological parameters, body composition and bone age. Patient reported outcome (PRO) measures include, but are not limited to, Short Form 12 in adults and adolescents aged 14 years and over. Safety reporting includes adverse events.

**Conclusions:**

The registry documents children and adults in one joint registry, includes, at present, patients in Germany and allows documentation of patients on all approved somatropin and other growth hormone preparations. It will allow to describe the transition of subjects from adolescence to adulthood (treatment and height), to describe switches between somatotropin preparations, to perform responder analyses, and to analyse differences and similarities of somatropin utilization (by age group, sex, setting, and PRO instrument). INSIGHTS-GHT offers a broad, comprehensive research platform to assess multiple relevant aspects of somatropin treatment and outcomes (including the transition of subjects from adolescence to adulthood), allows the documentation of all GH products including long-acting GH preparations after their introduction, and will evaluate the data independently of funders.

*Trial registration* BfArM Nr. NIS7492, DRKS registry DRKS00027394.

## Background

Growth hormone (GH), Secreted by the anterior pituitary gland, plays a pivotal role in growth and metabolism.

In pediatric patients (infants, children and adolescents) growth hormone deficiency (GHD) is a rare condition that may occur due to various causes. Subdivisions of GHD include isolated and multiple pituitary hormone deficiency, congenital (present from birth), acquired (e.g., due to tumour, result of radiation damage, infection, trauma), and idiopathic forms (no known cause). The conditions may result in infantile hypoglycaemia, growth retardation and short stature, and maturation delays reflected by the delay of lengthening of the bones of the extremities that is inappropriate to the chronological age of the child. There is also a prescribability for supraphysiological non-replacement GH for some other indications with short stature. The term “small for gestational age” (SGA) generally describes any infant whose birth weight and/or length is less than -2 SDS (standard deviation score, related to gestational age). Prerequisites for GH therapy for these children include a lack of spontaneous catch-up growth until the 4th birthday, a body height below 2.5 standard deviations (− 2.5 SDS) and a height velocity SDS for chronological age below zero (HV-SDS < 0). Turner syndrome is a sex-chromosomal disorder affecting 1 of 2500 females and is frequently characterized by short stature and additionally in most cases by the lack of spontaneous puberty. Prader–Willi syndrome (PWS) is a genetic disorder characterized by low muscle tone, short stature, incomplete sexual development, and a chronic feeling of hunger that, coupled with a metabolism that utilizes fewer calories than normal, can lead to excessive eating and life-threatening obesity [1]. Growth disorders in chronic renal insufficiency (CRI) also may require GH treatment (GHT). Short stature in PWS and CRI results, among other possible causes, from abnormalities of the GH–IGF axis.

In adults, GHD is associated with increased visceral adiposity, decreased lean body mass, bone mineral density and exercise capacity, dyslipidaemia, insulin resistance, increased cardiometabolic and fracture risk, and impaired quality of life [2]. Adult GHD can persist from childhood, or occurs due to structural lesions such as pituitary adenomas and other tumours of the sellar region, radiotherapy to the pituitary, traumatic brain injury and other rare causes [3].

Typical treatment of GHD due to the named conditions in children and adults is daily injection of recombinant GH. A number of products have been licensed in various indications. Furthermore, since 2022 EMA has approved long-acting GH preparations for the treatment of GHD. A large body of evidence has been gathered on the efficacy/effectiveness and safety of these substances, both from randomized controlled trials and from observational research [4–9]. Yet, there are many open research questions that can only or preferably be addressed by further observational research.

## Aims

The present registry aims to provide comprehensive information on different aspects of somatropin treatment in Germany within routine clinical practice: utilization, efficacy, safety, quality of life and other patient related outcomes (PRO), and economic variables, including post-treatment follow-up in various approved indications.

The registry documents children and adults in one joint registry, includes, at present, patients in Germany and allows documentation of patients on all approved somatropin and other growth hormone preparations.

It will allow to describe the transition of subjects from adolescence to adulthood (treatment and height), to describe switches between somatotropin preparations, to perform responder analyses, and to analyse differences and similarities of somatropin utilization (by age group, sex, setting, and PRO instrument).

The newly initiated registry INSIGHTS-GHT can document all indications for GH therapy in the context of the introduction of new therapies and complement the data from randomised controlled trials. It may serve quality assurance purposes, as individual centres can compare their results with other centres and with guideline recommendations.

## Methods

### Objectives and endpoints

The objectives and corresponding endpoints of the registry are shown in Table 1.

**Table 1 Tab1:** Objectives and endpoints

	**Objective**	**Endpoints**
**Primary**	To analyse somatropin drug utilization within routine clinical practice in a diverse population of children and adults, across all GH products To determine the place of long-acting GH in practice	Utilized GH preparations Dose and dosing schedule (daily vs. long-acting) Duration of treatment Persistence Switches between GH treatments Interruption/ discontinuation of GH treatment
**Secondary**	**Efficacy** To describe the long-term efficacy of somatropin To assess the transition from adolescence to adulthood	Paediatric indications: Real final adult height (using stadiometer) Adult indication: Body composition (all methods) Delta IGF-I standard deviation score (SDS, change during treatment / normalization) Delta height standard deviation score (SDS) / delta lean body mass Body proportions (sitting height; standing height), Delta target height vs height SDS Lipid status, inflammation markers, IGF-I, blood pressure Analyses stratified according to different diagnosis groups
	Persistence	Persistence calculated as duration of time from initiation to discontinuation of therapy
	Patient related outcomes (PRO) To describe patient PRO, including quality of life and patient experience over the initial 2 years of GH treatment, cross-sectional and long term (children and adults)	Satisfaction with treatment experience Quality of life, e.g., by SF-12 (in adults and adolescents) Additional validated self-reported or observed (e.g., parent- or partner-rated) QoL and PRO questionnaires can optionally be used
	**Safety** To describe the long-term safety of somatropin	Number and rate per patient-years of Adverse events All causally related and/or temporally associated AEs
**Exploratory**	Exploratory: To assess / analyse additional parameters potentially modulated by GHT To assess subgroups of the population under observation, or to assess outcomes by participating centres	e.g., body composition by DXA

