### Ethical aspects and data protection

#### Ethical approval

The registry is conducted consistent with consensus ethics principles derived from international ethics guidelines including the Declaration of Helsinki, and applicable local regulatory requirements and laws.

Prior to any data collection under this protocol, written informed consent with the approved ICF is obtained from the patient or patient’s legally authorized representative, as applicable, in accordance with local practice and regulations.

Detailed information about the registry and that registry participation is voluntary will be explained to the patient. This information may be provided in a personal conversation, and alternatively via telephone or videoconference. The patient will be given sufficient time to consider whether to participate in the registry. The signed ICF will be retained with the registry records. A copy of the ICF, signed and dated by the patient, must be given to the patient.

The patient or its guardian can revoke registry participation at any time. Patients who have revoked their participation will not be replaced.

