### Characteristics of patients

The eligible registry population will consist of children and adults of any age and of all sexes (male, female, diverse).

There is no formal screening procedure for suitable patients. Physicians are requested to assess all patients receiving somatropin products (already treated or newly to be initiated) for potential suitability for inclusion in the registry.

Patients are eligible for documentation if they.Are treated with any approved somatropin product,Are treated within the labelling of the respective product,Are available for long term follow-up documentation,(Or their parents/guardians, respectively) have provided informed consent.

Patients may change the somatropin product at any time, also repeatedly, during the course of documentation.

Patients are not eligible if they concurrently participate in a GH-related controlled clinical trial.

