### Safety reporting

The following safety data must be reported, if any of these events occur in patients treated with a GH product:Serious Adverse Events (SAE)Non-serious Adverse Event (AE)Reports of drug exposure during pregnancyReports of misuse and abuse of productsReports describing the occurrence of other “special circumstances” and “Special scenarios” (irrespective of whether a clinical event has occurred)

AEs are defined as follows: [10]

An untoward medical occurrence after exposure to a medicine, which is not necessarily caused by that medicine. An AE can therefore be any unfavourable and unintended sign (including an abnormal laboratory finding, for example), symptom, or disease temporally associated with the use of a medicinal product, whether or not considered related to the medicinal product.

SAEs are defined as follows: [10]

Any AE or experience that, at any dose,Results in deathIs life-threateningRequires hospitalization or prolongation of existing hospitalizationResults in permanent or serious disability/incapacityIs a congenital anomaly/birth defectIs a medically significant

Medical and scientific judgement should be exercised in deciding whether expedited reporting is appropriate in other situations, such as medically significant events that may not be immediately life-threatening or result in death or hospitalization but may jeopardize the patient or may require intervention to prevent one of the other outcomes listed in the definition above. These should also usually be considered serious.

Definition special scenario:

Includes reports of drug-drug/drug-food interaction, drug use during lactation or breast-feeding, lack of effectiveness, overdose, drug maladministration or accidental exposure, dispensing errors/medication errors, withdrawal or rebound symptoms, irrespective of whether a clinical event has occurred.

“Special Circumstances” mean drug exposure during pregnancy, drug misuse and abuse.

Pregnancies in women receiving GHT must be reported in the same way as AEs. The investigator will follow-up pregnancies to determine outcome (including premature termination) and status of mother and child and report it.

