### Descriptive analysis and statistical testing

Data will be analysed in regular (e.g., six months) intervals. This will be done to keep sites appraised of the progress of the registry and to review data quality (rate of missing values; data distribution, outliers).

All background variables and outcome parameters will be analysed descriptively with appropriate statistical methods: categorical variables by frequency tables (absolute and relative frequencies) and continuous variables by summary statistics (i.e., mean, standard deviation, minimum, median, quartiles and maximum). Continuous variables will also be described by absolute value and as change from baseline per analysis time point, if applicable.

Analyses will be performed for the total study population (overall analysis) and separately by indication or relevant subgroups (e.g., age, sex, GH pretreated and treatment-naive patients), if patient numbers are sufficient. Pretreated patients are here defined as patients already on treatment when enrolled in the study, whereas treatment-naive patients will be patients newly starting GHT.

The Statistical Analysis Plan (SAP) will specify details of the analysis.

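### The overall adverse event rate per patient-year mixes early and late GH treatment time in proportions set by enrolment, and the pretreated/naive split only partly separates them

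*Protocol article*

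**What the plan says.** The safety objective in Table 1 (Objectives and endpoints) reads "To describe the long-term safety of somatropin", and its endpoint is "Number and rate per patient-years of Adverse events". Table 1 also lists related and temporally associated AEs, but gives no time window or split by time on treatment for safety.

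The abstract's Methods make patients eligible "if they are on ongoing or newly initiated treatment with any approved somatropin or somatropin-related product within the labelling". Characteristics of patients repeats that both kinds of patient are to be considered ("already treated or newly to be initiated"). The article gives neither the expected share of each nor the length of prior treatment.

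On the start of AE capture, Ethical approval states: "Prior to any data collection under this protocol, written informed consent with the approved ICF is obtained". Under Visit schedule and assessments, each visit covers the time since the previous documentation. Safety reporting defines the trigger as "The following safety data must be reported, if any of these events occur in patients treated with a GH product", without a start date. The Inclusion Visit list records earlier GH products with start and stop dates and the reason for stopping, and also earlier diseases. It has no item for AEs during earlier GH treatment.

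Descriptive analysis and statistical testing plans results for the whole population. It also plans separate results by indication and subgroup, including pretreated versus treatment-naive, where the groups are large enough. Pretreated means on GH at enrolment, whatever the duration; naive means newly starting.

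**The concern.** A patient who enters after several years on GH contributes no early treatment time. A patient who stopped early because of an AE and never restarted cannot enter as an ongoing user. An overall rate per patient-year therefore averages over treatment periods with weights set by who was enrolled. If the AE rate changes with time on GH, two registries with identical underlying risks but different shares of new starters would report different rates, and so would two subgroups within this registry.

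The planned split does not put patients on the right time axis. It classifies them once, at enrolment. The pretreated class can run from weeks to many years of prior GH, and the naive class moves into later treatment time as follow-up proceeds. What is at stake is how the headline safety rate may be read, and whether subgroup differences in AE rates can be interpreted.

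**Working it through.** **Inputs from the article.** N = 1500 and a median observation of 2.5 years (Sample size).

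**Inputs assumed, because the article gives none.** The early window is the first year on GH. The later AE rate is set to 1 and the first-year rate to k. A share p of patients is already past year 1 at inclusion; the rest are followed from GH start. Every patient is observed for 2.5 years.

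**1. The plan's own figures.** The rule of three gives 3/1500 = 1/500 for one year each, and 3/(1500 × 2.5) = 3/3750 = 1/1250 for 2.5 years. Both stated figures reproduce. The second counts all person-time alike, whatever the time since GH start.

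**2. First-year person-time.** Only new starters supply it: 1500 × (1 − p) person-years.
- p = 0.5: 750 person-years, rule-of-three limit 3/750 = 1/250.
- p = 0.9: 150 person-years, limit 3/150 = 1/50.

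For an event confined to the first year, the 1/1250 figure therefore does not apply.

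**3. Drift within the naive class.** Of 2.5 years, 1.5 fall after year 1: 1.5/2.5 = 60%.

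**4. Effect of the enrolment mix.**
- Rate in a cohort followed from start: S = (k + 1.5)/2.5.
- Pooled rate: R = p + (1 − p) × S.

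| k | p | S | R | R relative to S |
|---|---|---|---|---|
| 1 | any | 1.00 | 1.00 | no difference |
| 2 | 0.5 | 1.40 | 1.20 | 14% lower |
| 3 | 0.7 | 1.80 | 1.24 | 31% lower |
| 5 | 0.9 | 2.60 | 1.16 | 55% lower |

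For k below 1 the sign reverses. With k = 0.5 and p = 0.5, S = 2.0/2.5 = 0.80 and R = 0.5 + 0.5 × 0.80 = 0.90, so the pooled rate is higher.

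**5. Which comparator is fair.** Against the first-year rate itself, the pooled rate is 40% lower at k = 2, p = 0.5 (1.20 vs 2) and 77% lower at k = 5, p = 0.9 (1.16 vs 5). A cohort made up entirely of new starters would already be 30% lower (1.40 vs 2) and 48% lower (2.60 vs 5), simply because follow-up runs beyond year 1. The part due to enrolling ongoing users is the one in step 4.

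**The case against.** The strongest reply is that banding of person-time is analysis-plan content. The article leaves calculated variables and tables to a SAP that is not shown, and Table 1 does not rule out banding. New and ongoing users are already to be analysed separately, and the stated aim is long-term safety, not the risk of a patient starting GH. The pretreated share, prior durations and early-to-late rate ratio are all unstated. Past treatment is not blank either, since stop reasons and earlier diseases are recorded.

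Much of this stands. The article contains no error here, and the SAP may already do what is suggested. But the article does fix a rate endpoint and a two-class definition at enrolment, and that definition does not separate early from later time in either class. A long-term rate still mixes the two in proportions set by enrolment. Stop reasons and earlier diseases give no rate for the earlier period.

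A reader might go further and infer that the rate mainly covers late treatment time, that it understates early events, or that recently approved long-acting products will show higher rates because their users are new starters. The documents support none of these. They give no mix and no early AE rate. They plan no comparison of AE rates between products. They also follow switches between preparations, so users of long-acting products may be long pretreated.

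**Conclusion.** The concern holds in a limited, conditional form. The overall AE rate depends on the enrolment mix whenever AE rates vary with time since GH start, and the planned split addresses this only in part. Capture of AEs from inclusion is a fair inference from the consent rule, the visit window and the inclusion list; the article states no start date.

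The 14% to 55% range is an illustration. It rests on a first-year rate 2 to 5 times the later one, 50% to 90% of patients past year 1 at inclusion, and a common 2.5 years of observation. Equal rates give no effect, and a lower early rate reverses it. The shortfall of 40% to 77% against the first-year rate should not be attributed to ongoing users, because 30 of the 40 points and 48 of the 77 would arise even in a cohort of new starters only. This is a worthwhile improvement to the analysis, not a demonstrated bias of known size.

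**What to change.** Keep the overall and pretreated/naive rates, and add one table to the SAP. Split each patient's observed time by time since first GH start, for example under 1 year, 1 to 3 years and over 3 years. Let patients enter at the band they have reached at inclusion (delayed entry). Report AE counts, patient-years and rates with 95% CI per band. Make any subgroup comparison of AE rates within band.

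The former and current GH start and stop dates needed for this are already collected, so the cost is SAP wording and one table. The downside is wider intervals per band than for the pooled rate. Banding cannot recover patients who stopped GH before they could be enrolled, and the report should state that as a limitation.

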### Ethical aspects and data protection

#### Ethical approval

The registry is conducted consistent with consensus ethics principles derived from international ethics guidelines including the Declaration of Helsinki, and applicable local regulatory requirements and laws.

Prior to any data collection under this protocol, written informed consent with the approved ICF is obtained from the patient or patient’s legally authorized representative, as applicable, in accordance with local practice and regulations.

Detailed information about the registry and that registry participation is voluntary will be explained to the patient. This information may be provided in a personal conversation, and alternatively via telephone or videoconference. The patient will be given sufficient time to consider whether to participate in the registry. The signed ICF will be retained with the registry records. A copy of the ICF, signed and dated by the patient, must be given to the patient.

The patient or its guardian can revoke registry participation at any time. Patients who have revoked their participation will not be replaced.

### Confidentiality and data protection

The sponsor as well as all investigators ensure adherence to applicable data privacy protection regulation. Data are transferred in encoded form only. The entire documentation made available to the sponsor does not contain any data which, on its own account or in conjunction with other freely available data, can be used to re-identify natural persons. The investigators are obligated to ensure that no documents contain such data.

All records identifying the subject will be kept confidential and will not be made publicly available. Patient names will not be supplied to the sponsor. If the patient’s name appears on any document, it must be obliterated before a copy of the document is supplied to the sponsor. Registry findings stored on a computer will be stored in accordance with local data protection laws.

The investigator will maintain a list to enable patients’ records to be identified in case of queries. In case of a report of a serious adverse drug reaction (SADR), the responsible pharmacovigilance person may ask for additional clarification. In that case, the company is not allowed to directly contact the patient. All additional information will be provided by the investigator.

Data protection rules will be closely followed and the standards of the General Data Protection Regulation (GDPR) will be met. Neither initials nor the exact birth date of the patient will be recorded in the database. Patient data are collected under a pseudonym. Upon saving of the first assessment (= inclusion visit), the EDC system automatically assigns a unique and consecutive Subject Identification Code (SIC). All registry documents (e.g., print outs of electronic case report forms, the informed consent forms etc. are identified with the SIC. The SIC alone cannot be used for identification of a given patient outside a site, in compliance with laws governing data privacy.

